## Abstract

**Background:**

Non-alcoholic fatty liver disease (NAFLD) affects 20–30% of the general adult population. NAFLD patients with type 2 diabetes mellitus (T2DM) are at an increased risk of advanced fibrosis, which puts them at risk of cardiovascular complications, hepatocellular carcinoma, or liver failure. Liver biopsy is the gold standard for assessing hepatic fibrosis. However, its utility is inherently limited. Consequently, the prevalence and characteristics of T2DM patients with advanced fibrosis are unknown. Therefore, the purpose of the current study is to evaluate the prevalence and severity of NAFLD in patients with T2DM by recruiting participants from primary care, using the latest imaging modalities, to collect a cohort of well phenotyped patients.

**Methods:**

We will prospectively recruit 400 patients with T2DM using biomarkers to assess their status.
Specifically, we will evaluate liver fat content using magnetic resonance imaging (MRI); hepatic fibrosis using MR elastography and vibration-controlled transient elastography; muscle composition and body fat distribution using water-fat separated whole body MRI; and cardiac function, structure, and tissue characteristics, using cardiovascular MRI.

**Discussion:**

We expect that the study will uncover potential mechanisms of advanced hepatic fibrosis in NAFLD and T2DM and equip the clinician with better diagnostic tools for the care of T2DM patients with NAFLD.

*Trial registration:* Clinicaltrials.gov, identifier NCT03864510. Registered 6 March 2019, https://clinicaltrials.gov/ct2/show/NCT03864510.

**Supplementary Information:**

The online version contains supplementary material available at 10.1186/s12876-021-01763-z.

## Background

Non-alcoholic fatty liver disease (NAFLD) is the most common chronic liver disease, with a worldwide prevalence of 20–30% [1]. Histological features range from hepatic steatosis to non-alcoholic steatohepatitis (NASH), the latter being characterized by inflammation, with or without fibrosis, with the risk of progressing to cirrhosis [2]. Cirrhosis, in turn, is associated with a 2.5% annual risk of developing hepatocellular carcinoma (HCC) [3]. In the near future, NAFLD is expected to become the leading cause for liver transplantation [4].

NAFLD increases the risk of liver-related and cardiovascular morbidity and mortality [5, 6]. Clinical and histological variables that predict overall mortality in NAFLD are age, type 2 diabetes mellitus (T2DM) [7, 8], and liver fibrosis [7, 9, 10].

In the last four decades, there has been a steep increase in T2DM global prevalence, both in high/middle-, and low-income countries [11]. And although NAFLD is strongly associated with the metabolic syndrome and T2DM [12], the association is bidirectional; with a markedly higher prevalence of NAFLD in patients with T2DM (40–70%) than in individuals without T2DM, and an increased incidence of T2DM in patients with NAFLD [13, 14].

Liver biopsy is the current gold standard for diagnosing severity of NAFLD. However, it has several limitations, including adverse events as well as sampling and observer variability [15–17]. Consequently, non-invasive methods are being evaluated to replace liver biopsy. These include magnetic resonance (MR)-based methods and serological marker testing.

Recently, the European Association for the Study of Diabetes (EASD), Obesity (EASO) and the Liver (EASL) proposed non-invasive screening for NAFLD and advanced fibrosis among patients with T2DM [18]. Nevertheless, to date, there is no clear consensus on how to implement these guidelines. Furthermore, concerns have been raised on whether screening is cost-effective, especially since most available non-invasive tests have low positive predictive value and because treatment of liver fibrosis is lacking [19].

Hepatic fat can be assessed directly by proton density fat fraction (PDFF) using magnetic resonance techniques [20, 21]. However, hepatic fibrosis has no molecular signature that can be detected and is therefore assessed indirectly by quantification of liver “stiffness” (or “elasticity”) [20]. The most accurate non-invasive methods for assessing stiffness include transient elastography (TE) and MR elastography (MRE).

Serological markers for the evaluation of liver fibrosis are more accessible and easier to use than imaging and therefore preferable for the evaluation of a prevalent disease. However, no panel of serological fibrosis markers has shown clinically acceptable sensitivity required for the diagnosis of advanced fibrosis although they can be used to exclude advanced fibrosis [24].

Most NAFLD-studies in patients with T2DM have been performed at tertiary centers where patients are more likely to have advanced NAFLD. In Sweden, most patients with T2DM is cared for in primary care. Hence, hospital series of NAFLD in T2DM patients is misleading. Therefore, we aim to recruit study participants from primary care, using the latest imaging techniques, to collect a cohort of well phenotyped patients with T2DM to evaluate the prevalence and severity of NAFLD in primary care.

## Methods/design

### Overview

The EPSONIP (**E**valuating the **P**revalence and **S**everity **O**f **N**AFLD in **P**rimary Care) study is a prospective cohort study with the aim to recruit 400 highly phenotyped patients with T2DM from primary care that will facilitate cross-sectional as well as longitudinal and long-term analyses. The comprehensive study protocol includes clinical information, fitness assessment, physical activity in everyday life, magnetic resonance imaging, lifestyle, and quality of life (QoL) data, as well as a biological sample collection (including genetic analysis). Specifically, we will evaluate liver fat content using magnetic resonance imaging (MRI); hepatic fibrosis, using magnetic resonance elastography (MRE) and vibration-controlled transient elastography (VCTE); fat free muscle volume, muscle fat infiltration, and abdominal fat distribution, using whole body fat–water separated MRI; and cardiac function and structure, using cardiovascular MRI (cardiovascular MRI will be assessed in 200 participants). Each participant will be investigated twice, at 3-year intervals, to identify individuals that develop cardiovascular disease and comorbidities, as well as progressive liver disease. See Fig. 1 for an overview of study procedures.

**Fig. 1 Fig1:**
[figure not shown]
Study flow chart outlining patient recruitment, inclusion, data collection and follow-up. CLD, chronic liver disease; MRI, magnetic resonance imaging; NAFLD, non-alcoholic fatty liver disease; T2DM, type 2 diabetes mellitus; VCTE, vibration controlled transient elastography

### Objectives

The overall purpose of the study is to better characterize the T2DM-NAFLD patient population using non-invasive methods to inform the diagnosis and care for this population. We aim to do this by identifying the relationship between T2DM, NAFLD, advanced hepatic fibrosis and myocardial dysfunction, as well as clinical, biochemical, and lifestyle parameters of patients with T2DM and NAFLD.

#### Specific aims

To determine the prevalence and incidence of NAFLD and advanced fibrosis in participants with T2DM using advanced non-invasive approaches.To test whether serological markers enable a faster and better-informed assessment than liver biopsy of the risk of advanced hepatic fibrosis, myocardial fibrosis, or myocardial dysfunction in participants with T2DM.To identify the clinical, biochemical, putative pathophysiological, and genetic factors associated with NAFLD and advanced fibrosis in participants with T2DMTo determine the relationship between NAFLD, myocardial function, and clinical, biochemical, and lifestyle factors in patients with and without T2DM.To identify non-invasive biomarkers that predict fibrosis progression and altered myocardial function in NAFLD patients with and without T2DM.

### Organization and oversight

The study is run and coordinated by [name] (PI) at the Department of Gastroenterology and Hepatology, University Hospital in Linköping, and Faculty of Medicine and Health Sciences, Linköping University. The study will be monitored by Forum Östergötland.

Patients will be recruited at primary healthcare centers. At present, four healthcare centers in South East Sweden (in Östergötland) are part of the study (Ekholmen and Kärna in Linköping, and Åby, Helsa Vårdcentral Kneippen and Cityhälsan Söder in Norrköping). Patient recruitment at each health care center will be overseen by General Practitioners participating in the study. The PI will supervise activities during regular on-site meetings. Collection of clinical data and blood samples will be performed by experienced research nurses. MRI will be performed at Center for Medical Image Science and Visualization (CMIV) in Linköping and the Department of Radiology at Vrinnevisjukhuset in Norrköping.

### Ethics approval and consent to participate

All recruitment and attaining written informed consent are conducted according to nationally accepted practice and in full accordance with the World Medical Association of Helsinki 2018. Data is collected and processed in accordance with the applicable General Data Protection Regulation (EU) 2016/679 (GDPR) legislation, and in compliance with the International Conference of Harmonization—Good Clinical Practice (ICH-GCP) requirements [22].

The EPSONIP study was approved by the Regional Ethical Board of Östergötland 2018/176-31 and 2018/494-32 and is registered as a clinical trial (clinicaltrials.gov identifier NCT 03864510). A complementary amendment, titled EPSONIP—Sleep, has been approved by the Swedish Ethical Review Authority 2019-03854.

### Participants

Patients with T2DM attending annual check-ups at their primary healthcare center will be eligible for inclusion in the study. Patients will be invited to participate by their diabetes nurse or treating physician. Patients of both sexes will be consecutively included. The inclusion and exclusion criteria are presented in Table 1

**Table 1 Tab1:** Inclusion and exclusion criteria

Criteria	
Inclusion	Diagnosis of T2DM according to current guidelines
	Age: 35–75 years
Exclusion	Contraindications to perform MRI (pacemaker, ferrous metal implants/fragments, claustrophobia, extreme obesity, and/or pregnancy)
	Alcohol dependence
	Previously diagnosed liver cirrhosis
	Previously diagnosed primary liver disease (except NAFLD)

Following receipt of information about the study and the opportunity to ask questions, participants will be asked to provide written informed consent, witnessed, and dated, by a member of the research team. Written informed consent will always be obtained prior to study-specific procedures.

### Estimation of sample size and power calculation

The cohort size was primarily defined so that a significant number of patients with significant or progressive fibrosis was identified. In previous studies of diabetic patients, 45–65% had fatty liver, and 7% had significant fibrosis [23]. Extrapolated to our study, that would give 260 patients with fatty liver and 28 patients with advanced fibrosis at baseline. At follow-up, one third of the patients with fatty liver is expected to progress in fibrosis stage. Therefore, we expect that approximately 86 patients will have a progressive disease state.

For the majority of our aims, no power calculation can be performed. But to ascertain that we had significant power to investigate non-invasive markers relevant for this patient cohort we made power calculations for one baseline and one follow-up parameter. Given the focus of the study on ectopic fat accumulation we wanted to ascertain that we had sufficient power to detect a difference in epicardial fat accumulation between diabetic patients with and without fatty liver at baseline. In a previous study performed by our group, patients with diabetes had an epicardial fat volume of 62.1 ± 21.0 mL/m^2^. We expect at least a 10% difference between groups. The power calculation indicated, with 80% power, that 90 patients would be sufficient to detect a difference at an α value of 0.05. For the follow-up assessment we decided to use end diastolic volume (EDV) as a surrogate for cardiac remodeling. In our patients with diabetes the EDV was 69.6 ± 15.2 mL/m^2^. We expect at least a 10% difference between groups. The power calculation indicated, with 80% power, that 146 patients would be sufficient to detect a difference at an α value of 0.05.

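### The 90 patients stated for the baseline epicardial-fat comparison do not follow from the stated inputs; for a 10% difference a two-group test needs about 361 to 397, and the 200 cardiac-MRI participants give 51–55% power

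*Protocol article*

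**What the plan says.** Under the heading on sample size and power, the protocol article says that power cannot be calculated for most aims and offers two calculations, one at baseline and one at follow-up.

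- **Baseline comparison:** the "difference in epicardial fat accumulation between diabetic patients with and without fatty liver at baseline".
- **Baseline inputs:** "patients with diabetes had an epicardial fat volume of 62.1 ± 21.0" mL/m², and "We expect at least a 10% difference between groups".
- **Baseline conclusion:** "with 80% power, that 90 patients would be sufficient to detect a difference", with α 0.05.
- **Follow-up:** end-diastolic volume (EDV), 69.6 ± 15.2 mL/m², again with a 10% difference, 80% power and α 0.05. The conclusion is "that 146 patients would be sufficient to detect a difference".

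The section also cites earlier diabetic series in which "45–65% had fatty liver, and 7% had significant fibrosis". Its own projection of 260 patients with fatty liver out of 400 uses the upper end, 65%.

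Two other places bear on the point. The Overview says that "cardiovascular MRI will be assessed in 200 participants". The section on the multimodal MR examination lists cardiac DIXON imaging, which provides the epicardial fat measurement, among the cardiac investigations.

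**The concern.** Every input needed to check the baseline figure is printed, and the comparison is plainly between two independent groups. Yet 90 is far too small for a standardised difference of about 0.3.

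The companion figure points the same way. Epicardial fat has the larger coefficient of variation (21.0/62.1 = 34%, against 15.2/69.6 = 22% for EDV). At the same relative difference, power and α it should need more patients than EDV, but it is given fewer (90 against 146).

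This is the only baseline power statement in the article. Taken at face value, 90 makes the 200 cardiac-MRI participants look like more than twice what is needed. If 10% is the intended difference, 200 is well short, and a null epicardial-fat result could be credited with a sensitivity the study does not have.

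**Working it through.** **Inputs.** From the sample-size section: mean 62.1, SD 21.0, difference 10%, power 80%, α 0.05, fatty liver in 45–65%. From the Overview: 200 with cardiovascular MRI. Assumptions: two-sided testing unless noted, the same SD in both groups, and the 45–65% range carried over to the 200 scanned.

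**Effect.** 0.10 × 62.1 = 6.21 mL/m². Standardised: d = 6.21/21.0 = 0.2957.

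**1. Reproducing 90.** Two routes give it.
- One-sample formula, 10% difference: n = [(1.960 + 0.842)/0.2957]² = 89.8, rounded up to 90.
- Two-group formula, 20% difference (12.42 mL/m², d = 0.591): n per group = 2 × [(1.960 + 0.842)/0.591]² = 44.9, so 45 per group and 90 in total.

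Both match because going from two groups to one sample, and doubling the difference, each divide the total by four. No two-group calculation at 10% gives 90, whether as a total or per group, one-sided or two-sided.

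**2. Size needed for the stated comparison at 10%.** With a fraction f having fatty liver, total N ≈ (1.960 + 0.842)² / [d² f(1 − f)]. The t-test adds about 2.

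| Fatty liver | N, normal formula | N, t-test |
|---|---|---|
| 50% | 359.0 | 361 |
| 45% | 362.7 | 365 |
| 65% | 394.5 | 397 |

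One-sided with equal groups, the t-test needs about 284.

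**3. Power if 90 were used, 10% difference.** With 90 in total: 28% (equal groups) or 26% (65:35). Reading 90 as per group (90 v 90): 51%.

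**4. Companion EDV figure.** d = 6.96/15.2 = 0.458. The two-group total is 150 (normal formula) or 152 (t-test), so 146 is close to a two-group total; the one-sample formula would give 37.4. Scaling 146 by the squared ratio of the coefficients of variation, 146 × [(21.0/62.1)/(15.2/69.6)]², gives 350 for epicardial fat. The two figures in the paragraph are therefore inconsistent if both use 10% and a like design.

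**5. What 200 scanned participants give for 10% (t-test).**

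| Split (with v without) | Two-sided power | One-sided power | Difference detectable at 80%, two-sided |
|---|---|---|---|
| 100 v 100 | 55% | 67% | 8.4 mL/m² (13.5%) |
| 90 v 110 | 54% | 67% | 8.4 mL/m² (13.5%) |
| 130 v 70 | 51% | 63% | 8.8 mL/m² (14.1%) |

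**6. If 20% was meant.** With 200 scanned, two-sided power is about 98% (98% at 130 v 70, 99% at 100 v 100). The total of 90 holds for near-equal groups; at 65:35 the normal formula gives 394.5/4 = 98.6, so about 99.

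**7. If all 400 had epicardial fat measured, 10% difference.** Power would be 80% (260 v 140) to 84% (200 v 200).

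**The case against.** A reader might infer that a one-sample formula was applied by mistake. The match is exact after rounding, but the document does not establish it. A two-group calculation for a 20% difference matches equally well, and since the EDV figure looks like a two-group total, a misprinted percentage is at least as plausible. In that case 200 is ample and only the percentage is wrong. This objection stands, and it decides the form of the fix.

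The EDV comparison is support rather than proof. The groups for the follow-up analysis are not defined, so scaling 146 to 350 assumes a like contrast and allocation.

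Sidedness is not stated. One-sided testing lowers the need to about 284 and raises power at 200 to 63–67%. That weakens the numbers but does not bring 200 up to 80%.

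The wording allows for a difference of at least 10%, so the true one could be larger. But 10% is the only value given to size on.

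A reader might also infer that the cohort of 400 is undersized or its justification void. The documents do not support that: its size was set primarily on expected numbers with fibrosis, and neither 400 nor 200 is said to derive from the 90. Nor does the abstract need to change, since the Overview already states the limit of 200.

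**Conclusion.** The point holds in this form: 90 patients do not give 80% power for the stated two-group comparison at the stated 10% difference. The requirement is about 361 to 397 in total two-sided, roughly four times the stated figure, and about 284 one-sided with equal groups. The cause of the discrepancy is undetermined.

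If 10% is the intended difference, the 200 cardiac-MRI participants deliver 51–55% power (63–67% one-sided) rather than the 80% claimed. If 20% was intended, the sample is adequate and the stated difference is the error. Either way the sentence needs correction.

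These figures rest on an SD of 21.0 in both groups, on 45–65% fatty liver among those scanned, and on epicardial fat being obtained only in the 200 with cardiovascular MRI, as the Overview and the MR section together indicate.

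**What to change.** First reconcile the effect size with the sample size from the original calculation, and state whether the test is one- or two-sided.

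- **If 10% stands:** delete the claim that 90 patients suffice and state instead: *With 200 participants undergoing cardiac MRI, assuming 45–65% have fatty liver, the study has 51–55% power (two-sided α 0.05) for a 10% (6.2 mL/m²) difference and 80% power for about 8.4–8.8 mL/m² (about 14%).*
- **If 20% was intended:** correct the stated difference to 20% (12.4 mL/m²). The total of 90 is then right for equal groups, and 200 gives about 98% power. Say that equal groups were assumed, since a 65:35 split needs about 99.

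The cost is wording only: no change to recruitment, imaging or the cohort of 400. Under the first option the stated power becomes less favourable; under the second, the expected difference becomes larger and needs its own justification.

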### Study procedures

Following the provision of informed consent, patients will be assigned a unique study-participate identification code incorporating the recruitment site identifier. All data will be link-anonymized throughout the study, recorded through a secure web-based application for electronic data (REDCap™).

Patients that have consented to participate in the study will participate in a subsequent study visit at one of two sites (Linköping or Norrköping). A member of the research team will complete a clinical report form on clinical data (Table 2), with special focus on T2DM history and treatment. Questionnaires regarding the lifestyle and self-reported quality of life will be obtained, fitness and physical activity will be assessed, and baseline clinical biochemistry will be obtained.

**Table 2 Tab2:** Layout of the anthropometric and clinical data collected at inclusion and 3 year follow-up

Categories of data	
Basic data	
Date of birth	
Gender	
Anthropometrics	
Height (cm)	
Weight (kg)	
Waist circumference (cm)	
Hip circumference (cm)	
Blood pressure (mmHg)	
Medical history	
Date of T2DM diagnosis	
Current or recent medication (including over-the-counter, traditional/herbal remedies, and nutritional supplements)	
Relevant comorbidities and date of diagnosis, including	
Hypertension, dyslipidemia	
Ischemic heart disease, including PCI and CABG	
Congestive heart failure	
Stroke	
Malignancies	
Lifestyle	
Smoking—yes/no/ex, and frequency of smoking (pack-years)	
Coffee consumption—cups/days	
Alcohol consumption	
Physical activity and fitness	
Patient reported quality of life	
Sleep quality assessment	
Family history	
Family medical history	

#### Questionnaires

Four validated questionnaires will be used to assess lifestyle factors relevant to NAFLD:Alcohol questionnairesAUDIT: The Alcohol Use Disorders Identification Test (AUDIT), a screening tool developed by the World Health Organization to assess alcohol consumption, drinking behaviors, and alcohol-related problems [24].LDH: Lifetime Drinking History, designed to provide quantitative indices of an individual’s alcohol consumption patterns from the onset of regular drinking [25].Lifestyle questionnaireDietary and physical activity variables are assessed using the validated questionnaires developed by the National Board of Health and Welfare in Sweden [26, 27].IFIS: The International Fitness Scale, to assess self-reported fitness [28].ESS: Epworth Sleepiness Scale [29].PSQI: Pittsburgh Sleep Quality Index [30].STOP-Bang: Obstructive sleep apnea questionnaire [31].Patient-reported quality of life.EQ-5D-5L: This questionnaire was developed by the EuroQol Group in 2009 as a measure of health-related quality of life. The descriptive system comprises five dimensions: mobility, self-care, usual activities, pain/discomfort, and anxiety/depression [32].

#### Fitness and physical activity

Lifestyle and NAFLD are closely related. Accordingly, we will perform an objective cardiorespiratory fitness measurement (6-min walk test) and a 7 day registration of objective physical activity using an accelerometer (Actigraph^®^ GT3X, Pensacola, FL, USA).The 6-min walk test is a submaximal functional exercise test that measures the distance walked over a period of 6 min [33]. The 6-min walk distance provides a measure for integrated global response of multiple cardiopulmonary and musculoskeletal systems involved in exercise, i.e., cardiorespiratory fitness.Physical activity over 7 d will be recorded using Actigraph^®^ GT3X, a small non-invasive accelerometer worn on the wrist, that captures and records continuous, high-resolution physical activity and sleep/wake information.One overnight registration of signs related to obstructive sleep apnea recorded by home respiratory polygraphy.

